## Methods

### Study design

This is a pilot randomised controlled trial (RCT) with an embedded qualitative study. We will follow the first two steps in the Sax Institute’s Translational Research Framework [31] to investigate the feasibility and preliminary efficacy of an online MBSR program for chronic musculoskeletal pain. This Translational Research Framework serves to bridge the gap between research and real-world implementation by systematically addressing barriers at different stages of translation. This study specifically focuses on two key translational steps: (1) T1 (feasibility testing): assessing the feasibility of the intervention in a controlled setting, including recruitment, adherence, and preliminary engagement outcomes; and (2) T2 (clinical research): assessing the preliminary efficacy of the intervention to determine its potential benefits. These steps provide a structured approach to evaluating the feasibility and preliminary efficacy of the online MBSR program for individuals with chronic musculoskeletal pain [32].

This study employs an exploratory sequential mixed-methods design, in which quantitative data will be collected first, followed by qualitative interviews to provide further insights into participants’ experiences. This approach enables the identification of key trends in the quantitative data, which can then be explored in greater depth through qualitative methods. The quantitative component will assess recruitment rates, intervention adherence, patient-reported outcomes, and adverse events, providing objective feasibility data. The qualitative component, gathered through semi-structured interviews, will explore participants’ experiences with the program, including barriers and facilitators to engagement, intervention acceptability (e.g. content, complexity, delivery, and areas for improvement), and key factors influencing future implementation and scalability. This integrated approach ensures a comprehensive evaluation of both feasibility and user experience, informing the design of a larger-scale trial. To ensure clarity and transparency in reporting, study findings will adhere to the CONSORT 2010 statement: extension to randomised pilot and feasibility trials [33]. The qualitative component will be reported following the Consolidated Criteria for Reporting Qualitative Research (COREQ): a 32-item checklist for interviews and focus groups [34].

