Potential participants who expressed interest in the study over the phone with one of the Clinical Nurse Consultants who did not complete the pre-screener survey will be sent a reminder email 3 to 5 days after the initial email. The reminder email will also mention that a research investigator may contact potential participants on their provided phone number to see if they have received this email and if they are still interested in learning more about the study.

If potential participants do not complete the pre-screener survey after the reminder email, a research investigator will call them 1 week after the initial contact from the Clinical Nurse Consultants to ask if they have received the email and if they are still interested in learning more about the study. This will be the last attempt to contact the participants. No further contact will be made if they are not interested. During the call, if they remain interested in the study, the research investigator will direct the potential participants to the email or re-send the email with the Participant Information Sheet, Consent Form and the pre-screener survey. Potential participants will also have the opportunity to ask questions about the study during the phone call.

If a potential participant who received a recruitment SMS and did not opt out of future communications about the study does not complete the pre-screener survey, they will be sent a follow-up SMS 5 days after the initial SMS. This will be the last attempt to contact the participants. No further contact will be made if they are not interested.

If eligible after completing the pre-screener survey, potential participants will receive a phone call from an experienced MBSR teacher and psychotherapist to screen for mental health concerns. During the phone call, the MBSR teacher will ask eleven questions to screen for any severe and uncontrolled mental health condition or a history of an unexplored, untreated traumatic experience. If eligible after completing the mental health screen, potential participants will be reminded that if they agree to participate in the study, they have a 50% chance of being in either the MBSR group or the usual care control group.

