##### Patient-reported outcome measures (PROMs)

Upon entry to the study, prior to randomisation, we will collect demographic information, including age, gender, race, ethnicity, education level, and postcode (to be used as a proxy for socioeconomic status). We will also collect information about the participant’s general health status and pain condition, including the number of years they have lived with chronic pain and their primary sources or locations of pain. Patient-reported outcome measures will be collected upon entry to the study prior to randomisation, and at the conclusion of the online MBSR program, to assess preliminary pre- to post-intervention changes. We will use the validated and widely used patient-reported outcome measures that make up the electronic Persistent Pain Outcomes Collaboration (ePPOC). The ePPOC is a resource for pain researchers and clinicians, which was established in NSW in 2013, to evaluate and assist in improving outcomes and services for people experiencing chronic pain [41]. The ePPOC measures pain and disability using the Brief Pain Inventory (BPI) [42], cognition using the Pain Self-Efficacy Questionnaire (PSEQ) [43], pain catastrophising using the Pain Catastrophising Scale (PCS) [44], mood using the Depression, Anxiety and Stress Scale (DASS-21) [45], health care utilisation and medication. These measures are recommended and used in pain management centres within Australia and New Zealand. We will also measure chronic pain acceptance using the Chronic Pain Acceptance Questionnaire (CPAQ) [46]. The CPAQ measures two aspects of chronic pain acceptance - activity engagement and pain willingness. Participants will be emailed a link to these questionnaires, which will be embedded into a web-based application (REDCap). The data collection process is illustrated in Fig. 2.

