##### Adherence to the mindfulness practice

Adherence to the suggested daily mindfulness practices throughout the 8-week intervention will be measured weekly via REDCap, using an online version of the Mindfulness Adherence Questionnaire (MAQ) [47]. The MAQ is a 12-item self-reported questionnaire that captures adherence to the mindfulness practice within the past week. It was designed to assess regular and sustained practice in attentional focus and non-judgmental acceptance (i.e. quantity, quality, subtype of practice). The first two items measure the frequency and average duration (in minutes) of formal practices. The remaining 10 items measure the quality of formal practice and informal practice. Items are scored on a 7-point Likert scale ranging from 0 (never) to 6 (always), with higher total subscale scores reflecting higher practice quality.

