##### Adverse events

The Meditation-Related Adverse Effects Scale - Mindfulness-Based Program version (MRAES-MBP) [48], will be used to collect data regarding adverse events. An email with a link to the MRAES-MBP embedded in REDCap will be sent to participants weekly. The MRAES-MBP scale represents the ten most common adverse events and those most highly associated with negative impacts on functioning, in the context of a mindfulness-based program, specifically: signs of hyperarousal (anxiety, perceptual hypersensitivity, traumatic re-experiencing, emotional lability, insomnia), hypo-arousal/blunting (anhedonia, depersonalisation), executive dysfunction and social disengagement [48]. If a participant reports experiencing distress that is impairing their ability to function, they will receive a phone call from our MBSR program teacher, who is an experienced Medical Doctor with extended skills in psychological medicine and a special interest in mindfulness-based interventions, complex trauma and the psychological aspects of chronic pain. Depending on the severity of the distress and the level of impact on functioning, the meditation practices may need to be adjusted or discontinued, or the participant may be advised to discontinue the intervention altogether. Where appropriate, the participant will be referred to the psychologist at the RPAH or CRGH pain management centres.

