### Ethics

This pilot RCT includes key methodological features to minimise bias in clinical trials, such as randomisation, concealed allocation, specification of eligibility criteria, blinded outcome assessment, blinded analysis, and intention-to-treat analysis. Data will be stored in spreadsheets and transferred to appropriate statistical software for analysis by an investigator blinded to group allocation. Spreadsheets will be regularly scrutinised for omissions and errors. Data will be stored and accessed as per the ethics requirements.

We will adhere to the Australian Code for the Responsible Conduct of Research for the storage and archiving of data. Data will be retained for 5 years with restricted access (the research data and/or metadata cannot be shared). All data files (e.g. audiotapes, transcripts) will be stored on a secure server at The University of Sydney, with access restricted to the study investigators. Data files will be coded. After 5 years of storage, the data will be securely destroyed. Electronic data will be deleted, and any paper copies will be shredded.

A Data Safety Monitoring Board (DSMB) will be convened to oversee this study. The board will be comprised of three members: an Associate Professor who is a psychologist, an Associate Professor who is a physician, and a senior physiotherapist who is the Director of Allied Health Services at one of the Sydney Local Health Districts and Co-Chair of the Musculoskeletal Network at the Agency of Clinical Innovation. The DSMB will have an initial meeting before the study commences. In this initial meeting, the DSMB will review the role and functioning of the DSMB, discuss the format and content of the DSMB reports and review scientific and ethical issues relating to the design and conduct of the trial. The DSMB will meet again at 4 weeks after the MBSR program commences and at the end of the 8-week program.

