### Study limitations

While this pilot study aims to assess the feasibility of an online MBSR intervention for individuals with chronic musculoskeletal pain, some limitations should be acknowledged. Selection bias may arise due to the requirement for English proficiency and internet access, potentially excluding individuals from lower socioeconomic backgrounds. This limitation will be explicitly discussed in the study’s findings interpretation, and future research should explore strategies to enhance accessibility, such as translated materials and mobile-based adaptations. The small sample size limits generalisability, as pilot studies are not powered to detect definitive treatment effects. Differences in engagement between online and in-person MBSR programs may also impact adherence, as digital interventions often experience higher attrition rates [56]. To mitigate this, we will implement structured reminders, participant check-ins, and engagement tracking. Additionally, expectation-related bias may influence adherence, as participants’ perceptions of treatment effectiveness can shape engagement levels [57]. To address these challenges, both groups will receive clear information on the exploratory nature of the study and its contribution to chronic pain research. Despite these limitations, this study will generate valuable feasibility data to refine the intervention and inform a larger-scale trial.

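### The Ethics section claims blinded outcome assessment, but PROMs, adherence and adverse events are all self-reported by participants who know their group; only the analyst is blinded

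*Protocol article*

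**What the plan says.** The Ethics section states that the pilot has several features that minimise bias, including "specification of eligibility criteria, blinded outcome assessment, blinded analysis". Its next sentence gives substance to the last of these, describing "analysis by an investigator blinded to group allocation".

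The outcome sections describe how data are obtained:

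- Patient-reported outcome measures: "Participants will be emailed a link to these questionnaires, which will be embedded into a web-based application (REDCap". The set is BPI, PSEQ, PCS, DASS-21 and CPAQ, with health care use and medication. It is collected before randomisation and again when the programme ends.
- Adherence: "The MAQ is a 12-item self-reported questionnaire that captures adherence to the mindfulness practice within the past week".
- Adverse events: "An email with a link to the MRAES-MBP embedded in REDCap will be sent to participants weekly".

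On awareness of allocation, the Pre-screening section says candidates are reminded that "they have a 50% chance of being in either the MBSR group or the usual care control group". The Intervention section compares weekly live online classes plus a workshop with usual waitlist care.

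On caveats, the Discussion asks for caution with patient-reported results because the trial is small and preliminary. Study limitations says that "expectation-related bias may influence adherence", and answers this by telling both groups that the study is exploratory.

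**The concern.** Blinded outcome assessment and blinded analysis are listed as two separate protections, so the first cannot be read as shorthand for the second. Blinded assessment is meant to stop knowledge of allocation from influencing the recorded outcome. When the participant fills in the form, the participant is the assessor, and blinding the analyst later does nothing about how the answers were given.

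At stake is the third aim, preliminary efficacy and safety against usual care. The Data analysis section plans between-group mean differences with 95% intervals and says the effect sizes and variability will help with the design and sample size of a full trial. A reader who takes the Ethics list at face value would credit that comparison with a safeguard it lacks. The caveats elsewhere do not correct this. Small size is a matter of precision, whereas differential reporting shifts the estimate itself.

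**Working it through.** The article states no figure on this point, so there is none to reproduce. The check traces each outcome to the person who supplies it and asks whether that person knows the allocation.

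| Outcome | Section | Supplied by | Aware of group? |
|---|---|---|---|
| BPI, PSEQ, PCS, DASS-21, CPAQ; health care use, medication | Patient-reported outcome measures | Participant, emailed REDCap link | Not at baseline; yes at end of programme |
| MAQ | Adherence to the mindfulness practice | Participant, weekly in REDCap | Yes |
| MRAES-MBP | Adverse events | Participant, weekly emailed link | Yes |
| Recruitment, retention | Feasibility outcomes | Study records | Not self-reported |

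**Count.** Named instruments: 5 patient-reported scales + 1 adherence questionnaire + 1 adverse-effects scale = 7. Completed by the participant: 7 of 7. Rated by anyone else: 0 of 7.

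**Awareness.** No sentence says that participants are unblinded; this is an inference from three facts. They are told beforehand that the arms are MBSR and usual care. One arm then attends live group sessions for 8 weeks. The other stays on waitlist care with access to education resources, and no sham or attention control is described. No participant could fail to know their arm.

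**Timing.** Baseline questionnaires precede randomisation, so knowledge of allocation cannot affect them. It can affect the end-of-programme answers, and the comparison between groups depends on those.

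**Other possible assessors.** Under Adverse events, the person who telephones a participant reporting impairing distress is the MBSR teacher, who delivers the programme and is not blind either. The independent interviewers belong to the qualitative study of the MBSR group and do not assess trial outcomes.

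**Blinding claimed against blinding described.** Assessor: claimed, but none described. Analyst: claimed and described.

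**Caveats.** The Discussion ties caution to size and stage. Study limitations ties expectation effects to adherence. Neither says that patient-reported outcomes or adverse events are reported by people who know their allocation.

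**The case against.** The strongest reply is that this is one inaccurate item in a generic list, in a pilot whose main focus is feasibility and acceptability. Much of that stands. The progression rule (80%, 60% and 40% retention) is counted from records and uses no patient-reported outcome. The analysis is descriptive and sets no efficacy threshold. The article never says participants are blinded, describes both arms openly, and urges caution with the patient-reported results. Participant awareness is unavoidable when a live class is compared with waitlist care, and self-report is the normal source for pain, mood and self-efficacy, so the design is not shown to be badly chosen.

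A second reply is that an article condenses a fuller protocol, which might name a blinded assessor. That would meet a complaint about missing detail. Here the article affirms a property that its own data collection rules out: no fuller text can make the participant who completes the form unaware of having attended the classes. If the authors mean only that staff handling the data are blinded, that is a different and weaker protection.

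What remains is that a stated protection is absent, for a comparison that the Data analysis section intends to use, and that the text elsewhere leaves the statement uncorrected.

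**Conclusion.** The statement is wrong as written, with moderate severity. The claimed protection is missing for 7 of 7 named instruments, and so for the whole efficacy and safety comparison. It is irrelevant to recruitment, retention and the decision to proceed. The conclusion rests on one inference, that participants know which arm they are in, which is safe for this comparison.

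The documents do not support several stronger readings that a reader might draw:

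- *That the go/stop decision is biased.* It uses retention only.
- *That the inflation of the effect can be quantified.* The documents give no size for reporting bias and no rule acts on an observed effect size, so any such figure would merely restate the assumption put in.
- *That a full trial will inherit the problem.* The Discussion says only that such a trial may be designed; its comparator and outcome assessment are not described.
- *That the Study design wording "providing objective feasibility data" is a second false claim.* It describes the quantitative component as a whole, recruitment rates included, in contrast to interviews, and says nothing about blinding.

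**What to change.** In the Ethics section, delete the item on blinded outcome assessment, confine the blinding statement to the analyst, and add a sentence saying that patient-reported outcomes, practice adherence and adverse events are self-reported by participants aware of their allocation.

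In the Discussion and Study limitations, extend the limitation on expectation and reporting bias from adherence to the patient-reported and adverse-event results. Stop presenting the message to both groups that the study is exploratory as addressing it: that message leaves participants as aware of their arm as before.

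No change to design, data collection or analysis is needed. The cost is a few sentences and a less favourable statement of bias protection.

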## Discussion

Chronic musculoskeletal pain is a global health challenge that causes a significant burden to individuals and society [1]. Despite continuous advancements in treatment approaches, the prevalence and impact of chronic musculoskeletal pain continue to rise, making it a public health priority [1]. This pilot study lays the groundwork for assessing the feasibility, acceptability, and potential efficacy of integrating an online MBSR program into the Australian public healthcare system, thereby offering hope for a more equitable approach to managing this highly prevalent condition. Despite the evidence supporting MBSR’s efficacy for chronic pain [21], MBSR remains largely inaccessible to patients with chronic musculoskeletal pain conditions within the Australian public healthcare system. Current MBSR programs in Australia are predominantly offered as private courses, often associated with high costs, thus excluding a substantial portion of patients.

Online MBSR programs have become a convenient and accessible alternative to traditional in-person training [25]. Our study will explore the feasibility of offering an online MBSR program to individuals on the waitlists of two pain management centres at two major metropolitan hospitals in Sydney, NSW, Australia. Our feasibility outcomes, such as our recruitment and retention rates, will explore participants’ willingness to engage with this mind-body approach. Our findings will also demonstrate which individuals with chronic musculoskeletal pain are receptive to online interventions and are willing to explore new avenues for pain management. While the primary focus of this pilot study is feasibility and acceptability, preliminary efficacy regarding patient-reported outcomes, including pain, disability, mood, self-efficacy, pain catastrophising, and quality of life, will also provide valuable insights. While the results of the patient-reported outcomes should be interpreted with caution due to the small sample size and the preliminary nature of this study, this process will be insightful as it will demonstrate the feasibility of our data collection methods. Our skilled MBSR teacher will be able to guide participants through potential challenges and ensure their safety and well-being during the program. Nevertheless, adverse events will be monitored closely, addressing a gap in the literature regarding the reporting of adverse events in mindfulness trials.

The qualitative component of this study will provide valuable insights into participants’ experiences, identifying both barriers and facilitators to engaging with the MBSR program. Understanding these factors is critical for refining the online intervention and optimising its acceptability and delivery in future trials and, ultimately, within the healthcare system.

This pilot study will serve as a foundation for potential future research that integrates MBSR into health services. Building on the lessons learned and insights gained from this study, a fully powered clinical trial may be designed and implemented, with a more extensive and diverse participant pool, to provide robust evidence regarding the effectiveness of online MBSR for chronic musculoskeletal pain in the Australian healthcare system context [30]. As we move forward, efforts to reduce health disparities and improve the quality of life for individuals with chronic musculoskeletal pain should continue to be a priority.

### Study limitations

While this pilot study aims to assess the feasibility of an online MBSR intervention for individuals with chronic musculoskeletal pain, some limitations should be acknowledged. Selection bias may arise due to the requirement for English proficiency and internet access, potentially excluding individuals from lower socioeconomic backgrounds. This limitation will be explicitly discussed in the study’s findings interpretation, and future research should explore strategies to enhance accessibility, such as translated materials and mobile-based adaptations. The small sample size limits generalisability, as pilot studies are not powered to detect definitive treatment effects. Differences in engagement between online and in-person MBSR programs may also impact adherence, as digital interventions often experience higher attrition rates [56]. To mitigate this, we will implement structured reminders, participant check-ins, and engagement tracking. Additionally, expectation-related bias may influence adherence, as participants’ perceptions of treatment effectiveness can shape engagement levels [57]. To address these challenges, both groups will receive clear information on the exploratory nature of the study and its contribution to chronic pain research. Despite these limitations, this study will generate valuable feasibility data to refine the intervention and inform a larger-scale trial.

